## Abstract

**Background:**

Recurrent implantation failure (RIF) brings great challenges to clinicians and causes deep frustration to patients. Previous data has suggested that prednisone may play a promising role in the establishment of pregnancy and help improve the pregnancy outcome in women with RIF. But there is insufficient evidence from randomized clinical trials that had adequate power to determine if prednisone can enhance live births as the primary outcome.

**Methods/design:**

This trial is a prospective, multicenter, randomized, double-blind, placebo-controlled clinical trial (1:1 ratio of prednisone versus placebo). Infertile patients with RIF who intend to undergo frozen-thawed embryo transfer (FET) after in vitro fertilization (IVF) or intracytoplasmic sperm injection (ICSI) or pre-implantation genetic testing for aneuploidy (PGT-A) will be enrolled and randomly assigned to two parallel groups. Participants will be given the treatment of prednisone or placebo from the start of endometrial preparation till the end of the first trimester of pregnancy if pregnant. The primary outcome is live birth rate.

**Discussion:**

The results of this study will provide evidence for the effect of prednisone on pregnancy outcomes in patients with RIF.

**Trial registration:**

Chinese Clinical Trial Registry, ChiCTR1800018783. Registered on 9 October 2018.

## Background

Nowadays, infertility affects 8–12% of couples at reproductive age and has become a global problem [1]. In vitro fertilization (IVF) is widely used and well received in couples with reproductive difficulties. However, despite the optimal use of reproductive technologies (such as controlled ovarian hyper-stimulation, assisted hatching, pre-implantation genetic testing, and frozen embryo transfer), implantation remains a rate-limiting step in IVF treatment. Implantation rate is reported to be about 25% when cleavage embryos are transferred and 40% when blastocysts are transferred, which indicates that many couples would remain infertile after multiple attempts at embryo transfer [2].

Recurrent implantation failure (RIF) refers to the clinical condition of failing to achieve a clinical pregnancy after several embryo transfers, which brings great challenges to clinicians and causes deep frustration to patients [3]. The prevalence of RIF varies from 10 to 20% and is difficult to estimate, due to the condition that there is yet no universally accepted consensus on the definition of RIF [2, 4, 5]. Failure of implantation can be attributed to embryo quality, endometrial receptivity, or both. While poor embryo quality is thought to be responsible for 30–50% of implantation failures, decreased endometrial receptivity is responsible for approximately two thirds of these failures [6, 7]. Thus, many interventions aiming at overcoming decreased endometrial receptivity have been proposed to improve pregnancy outcomes in women with RIF, but only a few are evidence-based [8, 9].

Prednisone is a common immunomodulatory agent, which can exert a range of positive effects on the treatment of autoimmune disorders as well as the establishment of early pregnancy [1, 10]. Studies have shown that prednisone could not only suppress uterine NK cells cytotoxicity and cytokine secretion in pre-implantation endometrium, but also stimulate the secretion of human chorionic gonadotropin (hCG) and promote proliferation and invasion of trophoblast [1, 6], suggesting that prednisone may have a considerable impact on embryo implantation and IVF outcomes. Prednisone is also believed to have minimal side effects [11], because only about 10% of the active substance will reach the fetus [12–14].

However, limited clinical trials have focused on the effect of prednisone on pregnancy outcomes. Also, the trials were either small-sized or non-randomized studies or with combined treatment regimens, which were insufficiently powered to draw a conclusion. Therefore, multiple researchers and clinicians have called for a full-scale and well-designed randomized controlled trial (RCT) to clarify whether prednisone could improve pregnancy outcomes in women with RIF [15].

## Methods/design

### Design and setting

This is a prospective, multicenter, randomized, double-blind, placebo-controlled clinical trial to evaluate whether the administration of prednisone could improve the live birth rate in patients with RIF. Eligible patients will be randomly assigned to the prednisone group or placebo group with a 1:1 ratio. A flowchart of the study design is illustrated in Fig. 1.

**Fig. 1 Fig1:**
[figure not shown]
Flowchart of the study design

Patients will be recruited from 8 hospitals in China. The study is conducted in accordance with the Declaration of Helsinki and Good Clinical Practice guidelines. The study protocol has been approved by the ethics committees at all hospitals. The trial was registered at the Chinese Clinical Trial Registry (ChiCTR1800018783; http://www.chictr.org.cn/edit.aspx?pid=31155&htm=4).

### Eligibility criteria

#### Inclusion criteria

The inclusion criteria are as follows:
Infertile women with a history of RIF, which refers to the failure to achieve a clinical pregnancy under one of the following conditions with all embryos transferred being of good quality (criteria of good-quality embryos are shown in Table 1):
Three or more embryo transfer cycles;Two embryo transfer cycles where the cumulative number of transferred embryos was no less than three;Women who intend to undergo frozen-thawed embryo transfer (FET) after IVF or intracytoplasmic sperm injection (ICSI) or pre-implantation genetic testing for aneuploidy (PGT-A);Women under the age of 38 when oocytes were retrieved;Women who have at least 1 good-quality blastocyst or 2 good-quality day-3 embryos for transferBe capable of giving informed consent.

**Table 1 Tab1:** Criteria of good-quality embryo

Embryo	Scoring system	Criteria of good quality
Blastocyst	Gardner	≥ 4 BC
Cleavage (day 3)	Puissant	7–10 cell 3; 4 or compact
	Peter	7–10 cell I; II or compact

#### Exclusion criteria

The exclusion criteria are as follows:
Women who are currently receiving any corticosteroid or immunosuppression treatment, such as hydroxychloroquine, cyclosporine, and azathioprine. Two months of washout period will be required prior to screening for patients on these agents;Women with known autoimmune diseases such as systemic lupus erythematosus (SLE), antiphospholipid syndrome, Sjogren’s syndrome, and scleroderma;Women who have been diagnosed with diseases affecting the uterine cavity, such as uterine malformation and submucous fibroids;Women or their partner with abnormal chromosome karyotype (not including chromosome polymorphisms);Women who have experienced recurrent pregnancy loss, defined by two or more failed clinical pregnancies documented by ultrasonography or histopathologic examination;Women with thin endometrium (< 6 mm before transfer);Women with contraindications to corticosteroid;Women with medical contraindications to assisted reproductive technology and/or pregnancy.

### Sample size

According to the meta-analysis published in 2013, the live birth rate was estimated to be 16.1% in women with 3 or more failed embryo transfer cycles [16]. In women with 2 or more failed embryo transfer cycles, the live birth rate varied from 15.5 to 29% [17–19]. It is reported that the combined administration of prednisone and low molecular weight heparin or aspirin can improve live birth rate by 10.8–14% [17, 20, 21]. In the present study, we plan to test the primary hypothesis of a difference of 10% in the live birth rate between the two randomization arms. In patients with RIF, we assume that the live birth rate will be 30% in the prednisone arm and 20% in the placebo arm.

For the sample size calculations, the two-sided significance level will be set at *α* = 0.05 and the statistical power will be calculated as 1 − *β* = 0.80. The ratio between groups will be 1:1. The minimum sample size will be 294 for each group, for a total of 588 participants. Taking into consideration a dropout rate of 15%, we expect to ultimately have a total of 692 enrollees.

### Randomization and blinding

All eligible subjects will be randomly assigned to one of the two study arms according to a computer-generated randomization sequence generated by the data coordinating center (DCC) with SAS software version 9.2 (SAS Institute, Cary, NC). The randomization will be stratified according to the stage of embryo (cleavage embryo or blastocyst). The randomization sequence will be kept strictly confidential by the DCC staff. Therefore, the researchers who are in charge of the enrollment have no access to the list. Study personnel are all blinded to the upcoming treatment group allocation.

The study medication (both prednisone and placebo) is manufactured by Xianju Pharmaceutical Co., Ltd. Except for the active ingredients, the rest of the excipient and the appearance and odor are exactly the same as prednisone. The packaging of study medication (both prednisone and placebo) is marked according to the randomization sequence. The packaging and tablets of prednisone and the placebo have the same appearance, which cannot be distinguished. Therefore, the participants and all research staff do not know the allocation until the end of the study. The quality of the placebo, such as contents and bacteria contaminations, was controlled rigorously according to the GMP standard.

### Screening

At the screening visit, patients who have been using corticosteroid or other immunosuppression treatment will be excluded. The trial and study plan will be declared to all participants, and eligible couples who are interested in participating will sign the written informed consent. All tests for preparation of IVF or ICSI or PGT-A have been done. Screening for possible causes of RIF such as parental chromosomal anomalies, uterine factors (hysteroscopy if necessary), hydrosalpinx, and immunological and thrombophilic factors including antinuclear antibody (ANA), anticardiolipin antibody (ACA), double-stranded DNA antibody (ds-DNA), β2-glycoprotein I antibody (β2GP1), and platelet aggregation test (PAGT), will be recommended. The standardized case report forms (CRFs) are completed to collect current medication status and previous medical history. A physical examination (height, body weight, waistline, hipline, blood pressure) is performed. A schedule of enrollment, interventions, and assessment is provided in the Standard Protocol Items: Recommendations for Interventional Trials (SPIRIT) figure (Fig. 2). The SPIRIT checklist is presented in Additional file 1.

**Fig. 2 Fig2:**
[figure not shown]
SPIRIT diagram for schedule of enrollment, interventions, and assessments

Safety assessment includes liver function; renal function; CBC; fasting blood glucose; insulin; t1, day of embryo transfer (ET); t2, 2 weeks after ET; t3, 5 weeks after ET; t4, 10 weeks after ET; t5, 28 weeks of gestation; t6, 37 weeks of gestation; t7, delivery; and t8, 6 weeks after delivery.

### Interventions

A total of 692 eligible subjects will be enrolled and equally randomized into two parallel treatment arms:
A)Prednisone arm: oral prednisone arm 10 mg q.m. orally;B)Placebo arm: oral prednisone-matched placebo q.m. orally.

After a recruitment period and randomization, the researchers will dispense the first bottle (100 tablets per bottle) of the corresponding drug (prednisone/placebo). Patients will be instructed to take two tablets for once a day orally in the morning, starting with the hormone replacement regimen for endometrial preparation. Participants will undergo the frozen-thawed embryo transfer (FET). If pregnancy is confirmed, the second bottle of corresponding drug will be dispensed on the day of pregnancy test and the medication will be continued till the end of the first trimester of pregnancy. If the failure of transfer or pregnancy loss occurred, the medication will be discontinued. The remaining tablets will be returned to researchers.

### Discontinuation criteria

Reasons for discontinuation of medication include, but are not limited to, the following: (1) participants who become pregnant spontaneously, (2) participants who have experienced serious complications or side effects, (3) participants who use prohibited drugs such as other glucocorticoids or immunosuppression drugs, (4) participants with thin endometrium (< 6 mm before transfer), and (5) participants who request to withdraw from the trial.

### Frozen-thawed embryo transfer

The endometrium is prepared with a hormone replacement cycle regimen. Estradiol valerate (Progynova, Delpharm Lille SAS, France) and/or estradiol tablets (Femoston, Abbott Biologicals B.V., the Netherlands) at a dose of 2–8 mg daily will be started on days 2–5 of the menstrual cycle or 28–35 days after long-acting GnRH-agonist suppression. When the thickness of the endometrium is enough (≥ 6 mm), luteal phase support will be added with vaginal progesterone gel (Crinone, Merck Serono) 90 mg daily and oral dydrogesterone (Duphaston, Abbott) 10 mg twice daily.

One blastocyst or two cleavage embryos will be transferred in each participant. All embryos transferred will be of good quality. The serum hCG test is performed after 2 weeks of transfer. If the patient is pregnant, luteal phase support will be continued until 8–12 weeks of gestation and follow-up will be continued to the end of pregnancy.

### Outcome and outcome assessments

#### Primary outcome

The primary outcome is live birth after frozen-thawed embryo transfer, defined as the delivery of any number of newborns at ≥ 28 weeks of gestation with signs of life.

#### Secondary outcomes

The secondary outcomes include biochemical pregnancy, clinical pregnancy, implantation, pregnancy loss, pregnancy and perinatal complication, birth weight, congenital anomalies, and other adverse events. Biochemical pregnancy is defined as serum β-hCG ≥ 10 mIU/mL measured 12–15 days after embryo transfer. Clinical pregnancy is defined as the detection of a gestational sac in the uterine cavity by a transvaginal ultrasound scan 35 days after embryo transfer. Implantation rate is calculated as the number of gestational sacs by a transvaginal ultrasound scan/number of embryos transferred.

#### Follow-up protocol

The first pregnancy follow-up will be at 12 weeks of gestation. The first-trimester pregnancy complications (including but not limited to miscarriage, ectopic pregnancy, hyperemesis gravidarum, or gestational trophoblastic disease) will be evaluated by reviewing medical records or by telephone. The study medication (prednisone/placebo) will be discontinued, and the date of drug withdrawal will be recorded.

The second pregnancy follow-up will be at 28 weeks’ gestation. The second-trimester pregnancy complications (including but not limited to abortion, prenatal test results, gestational diabetes, incompetent cervix, or premature rupture of membrane) will be followed up by telephone call.

The third pregnancy follow-up will be at 37 weeks’ gestation. The third-trimester pregnancy complications (including but not limited to preterm labor, intrauterine growth retardation, pre-eclampsia/eclampsia, premature rupture of membrane, placental abruption, or abnormality of amniotic fluid) will be followed up by telephone call.

The fourth follow-up time point will be at delivery. Participants will be required to notify investigators about the time of delivery. The delivery information (including gestational age, delivery mode, placenta abnormality, and/or delivery complications) and neonatal information (including gender, birth weight, birth defects) will be obtained by designed forms or by reviewing obstetric and neonatal medical records.

The fifth and final follow-up will be at 6 weeks after delivery. Postpartum information regarding complications of the mother (including but not limited to infection, postpartum depression, late postpartum hemorrhage) or the infant (including but not limited to neonatal jaundice, neonatal infection, neonatal respiratory distress syndrome, neonatal hospitalization, and neonatal death) will be followed up by telephone or by reviewing medical records.

During the follow-up period, adverse events and concomitant medications will be inquired and recorded every time. Participants who quit or are lost to follow-up will also be recorded.

#### Adverse events

Adverse events (AEs) refer to any untoward medical occurrences associated with the subject’s participation during the research period regardless of whether considered to be related to the study intervention or not. Serious adverse events (SAEs) are events that occur during the subject’s participation in research that meet any of the following criteria: death, life-threatening events, severe or persistent disability, requiring inpatient hospitalization or prolongation of existing hospitalization, neonatal death up to 6 weeks after delivery, congenital anomaly or birth defect, or any events deemed serious by the local principal investigator.

All AEs will be assessed and recorded in detail. All SAEs will be reported to the principal investigator in 5 days, and appropriate measures will be initiated. SAEs which are unintended and possibly associated with study interventions should be reported within 24 h. The ethics committee will determine whether the AE or SAE is likely to be associated with the study medication and whether it is necessary to break blinding codes.

### Data management

All of the investigators including physicians, nurses, and research assistants will attend a training workshop before the starting of the trial, to ensure the accuracy of outcome assessments and data collection. A protocol and standard operation procedures will be given to every investigator.

All data will be collected using a standard CRF and recorded in the electronic data capture system where participants’ personal information cannot be traced. The DCC is responsible for the monitoring tasks of the trial. The DCC and personnel of Ren Ji hospital will check the authenticity, accuracy, and integrity of the data from different sites regularly to ensure the quality of the collected data.

### Data analysis plan

The data will be analyzed by SPSS 21.0 (SPSS Inc., Chicago, IL, USA). Normally distributed continuous variables will be expressed as mean ± standard deviation with Student’s test for testing between-group differences. Non-normally distributed continuous variables will be expressed as medians and ranges with Wilcoxon’s rank-sum test for between-group differences. Categorical data will be described as frequency and percentage; differences in these measures will be assessed by the Pearson chi-square test, with Fisher’s exact test for expected frequencies less than 5. *P* < 0.05 will be considered significant.

The analysis will be conducted using intention-to-treat principles. The primary outcome, live birth rate, will be compared between two groups by the Pearson chi-square test. Secondary outcomes, such as rates of pregnancy and implantation, will be analyzed using the Pearson chi-square test. A per-protocol analysis will be performed according to the actual participants completing the entire trial. As a secondary analysis, we will fit a generalized linear mixed effect model with a logit link to compare the treatment arms with respect to the primary outcome of live birth, and binary secondary outcomes (e.g., rates of pregnancy and implantation), adjusting for factors such as randomization stratification of embryo stage, and other explanatory variables. A random intercept will be included to adjust for the correlation among patients within center.

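### Randomisation is stratified by embryo stage but the primary live-birth test is not: a valid, slightly conservative choice that can be improved at almost no cost

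*Protocol article*

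**What the plan says.** Under Randomization and blinding, the protocol article states: "The randomization will be stratified according to the stage of embryo (cleavage embryo or blastocyst". Embryo stage is the only stratification factor named; centre is not one.

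Under Data analysis plan, the analysis follows intention to treat and "The primary outcome, live birth rate, will be compared between two groups by the Pearson chi-square test". Binary outcomes are summarised as counts and percentages. A secondary analysis fits a mixed model with a logit link to live birth, adjusting for embryo stage and further unnamed variables, with a random intercept for centre.

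Under Sample size, the target is an absolute difference: "we plan to test the primary hypothesis of a difference of 10% in the live birth rate between the two randomization arms". The assumption is that "the live birth rate will be 30% in the prednisone arm and 20% in the placebo arm".

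**The concern.** An analysis should normally reflect the way patients were randomised. When arms are balanced within strata and the stratum predicts outcome, part of the outcome variation lies between strata and cannot contribute to the treatment contrast. The pooled Pearson variance still counts that part, so the standard error is a little too large. The test then rejects slightly less often than 5% under the null and has slightly less power than a stratified test on the same data.

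The article treats embryo stage as worth adjusting for, but only in the secondary model. That model works on the odds-ratio scale, whereas the hypothesis is a 10-point difference in proportions. At stake are a little power in the headline P value and a stage-adjusted estimate on the scale of the hypothesis. Validity is not at stake.

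**Working it through.** **1. Reproduce the plan's figure.** The inputs, all from Sample size, are: "the two-sided significance level will be set at *α* = 0.05"; "the statistical power will be calculated as 1 − *β* = 0.80"; rates of 0.30 and 0.20; and "The ratio between groups will be 1:1". The pooled two-proportion formula without continuity correction, with mean rate 0.25, is

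n = [1.960 × √(2 × 0.25 × 0.75) + 0.8416 × √(0.30 × 0.70 + 0.20 × 0.80)]² / 0.10²

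= [1.2002 + 0.5119]² / 0.01 = 293.2, so 294 per arm and 588 in total. Then 588 / 0.85 = 691.8, so 692. All three stated figures reproduce. This formula matches the planned unstratified chi-square, so sample size and primary test agree with each other.

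**2. How large might the gap between stages be?** The article gives no live birth rate by stage. Its only guide is in Background: implantation of about 25% for cleavage embryos and 40% for blastocysts. Secondary outcomes defines implantation per embryo transferred. Frozen-thawed embryo transfer specifies two cleavage embryos or one blastocyst. Assuming that the two embryos implant independently, the chance of at least one implantation per woman is

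- cleavage: 1 − 0.75² = 0.4375, about 44%;
- blastocyst: 40%.

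The per-woman gap is about 4 points, and it runs opposite to the per-embryo gap. The gap in live birth is unknown, so a range of 0 to 20 points is shown.

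**3. Approximate variance saving.** With blastocyst share s and gap g, the variance after stratifying, relative to the pooled variance, is about

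r = 1 − s(1 − s)g² / (0.25 × 0.75).

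For s = 0.5 and g = 0.05, r = 1 − 0.000625 / 0.1875 = 0.9967. For g = 0.20, r = 1 − 0.01 / 0.1875 = 0.9467. Multiplying by 588 gives the number of women with whom a stratified test would match the pooled one: 586 and 557, a saving of 2 to 31 women.

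**4. Simulation.** The setting is 400,000 trials per scenario, 294 per arm, arms balanced within stage, overall placebo rate 20% and a common 10-point difference. Results for an equal split between stages:

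| Assumed gap (points) | Power, Pearson | Power, stratified | Gain (points) | Type I error, Pearson | Type I error, stratified | Equivalent N |
|---|---|---|---|---|---|---|
| 0 | 80.28% | 80.29% | 0.0 | 5.06% | 4.98% | 588 |
| 5 | 80.26% | 80.35% | 0.1 | 5.01% | 5.00% | 586 |
| 10 | 80.40% | 80.75% | 0.4 | 4.90% | 5.02% | 580 |
| 15 | 80.68% | 81.51% | 0.8 | 4.61% | 4.96% | 570 |
| 20 | 80.97% | 82.41% | 1.4 | 4.35% | 5.02% | 557 |

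With a blastocyst share of 30% or 70%, the gain at a 20-point gap is 1.3 or 1.2 points. With 346 per arm (nobody lost), the largest gain is 88.06% − 86.88% = 1.2 points. A second simulation of the equal-split case gave about 1.5 points at a 20-point gap, so the upper end is best read as 1.4 to 1.5. If the treatment effect is instead a common odds ratio with placebo rates of 10% and 30%, power goes from 81.1% to 83.1%, a gain of 2.0 points.

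**5. Precision of the estimate.** If the rates were 30% and 20%, the half-width of an unadjusted 95% interval for the difference would be 1.96 × √(0.37 / 294) = 7.0 points, or 1.96 × √(0.37 / 346) = 6.4 points with all 692 women.

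**The case against.** The strongest defence is that nothing here is wrong. The Pearson test protects the type I error, the sample size was computed for that test, and its 80% power is met in every scenario. Embryo stage and centre are already adjusted for in a prespecified secondary model, and the article makes clear which analysis is primary. The largest gains need a 20-point gap between stages that no part of the article supports. All of this stands, and it is why the point is minor.

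Four stronger readings are tempting, but the document does not support them.

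- A reader might take the 25% and 40% implantation rates as a 15-point gap between strata. They are per-embryo rates; per transfer they suggest about 44% against 40%. Nor does the article say why stage was chosen as the stratifier.
- A reader might infer that the primary analysis yields no estimate of the difference. The percentages in each arm will be reported, and their difference follows by subtraction. What is not named is an effect measure with its interval. A full protocol or analysis plan that is not shown here may name one, so its absence is no finding by itself.
- A reader might infer that the primary test must also be stratified by centre. Centre is not a stratification factor, no calculation here tests that choice, and the secondary model already handles centre.
- A reader might fear that the primary and adjusted results could disagree. That is true of any such pair of analyses, and the stated order of primary and secondary settles which governs.

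One part of the defence does not stand. An explicitly unstratified primary test is a stated choice, so an unseen analysis plan does not explain it away.

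**Conclusion.** The point holds as a minor improvement. The primary test leaves out the one factor used to stratify randomisation and is therefore valid but slightly conservative if that factor matters. Under a common risk difference and gaps of 0 to 20 points, the loss is about 0 to 1.5 power points, and about 0.1 at a gap near 5 points. Under a common odds ratio it reaches about 2.0 points at the 20-point extreme. The type I error of the Pearson test falls from about 5% to about 4.4% over that range and is not inflated.

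These sizes rest on assumptions that the article does not supply: the share of blastocyst transfers (30% to 70% tried), the live birth rates by stage, and balance between arms within stage. The 4-point guide also assumes independent implantation and that implantation tracks live birth. The figures of 294, 588 and 692 are unaffected.

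**What to change.** Before unblinding, restate the primary analysis as a Cochran-Mantel-Haenszel test of live birth stratified by embryo stage as randomised. Report it with the Mantel-Haenszel risk difference and 95% confidence interval, so that the headline estimate is on the scale of the 10-point hypothesis. Keep the Pearson chi-square as a sensitivity analysis and the mixed model with its random centre intercept as secondary. Do not add centre to the primary stratification on this ground.

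The change needs no further patients or data, since stage is already recorded for randomisation. Its cost is a dated amendment to the analysis wording. The Discussion reports more than 500 women already enrolled, so the amendment should record that it was made without knowledge of allocation. Randomization and blinding keeps allocation concealed until the study ends, which makes that possible.

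### Implantation rate is counted per embryo, but its chi-square test and centre-only mixed model treat the two embryos of a cleavage-stage woman as independent

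*Protocol article*

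**What the plan says.** Four statements in the Protocol article, read together, fix the analysis of implantation.

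- **Definition** (Secondary outcomes): "Implantation rate is calculated as the number of gestational sacs by a transvaginal ultrasound scan/number of embryos transferred". The denominator is embryos.
- **Embryos per woman** (Frozen-thawed embryo transfer): "One blastocyst or two cleavage embryos will be transferred in each participant". A blastocyst participant contributes one unit and a cleavage-stage participant two.
- **Main test** (Data analysis plan): "Secondary outcomes, such as rates of pregnancy and implantation, will be analyzed using the Pearson chi-square test".
- **Secondary model** (Data analysis plan): a logit mixed model is also to be fitted to "binary secondary outcomes (e.g., rates of pregnancy and implantation), adjusting for factors such as randomization stratification of embryo stage, and other explanatory variables". On clustering it says only: "A random intercept will be included to adjust for the correlation among patients within center".

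The section Randomization and blinding allocates subjects, stratified by embryo stage; embryos are not allocated. The threshold for every test is P < 0.05.

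**The concern.** The Pearson chi-square test takes its variance from independent units. Two embryos placed in the same uterus, under the same allocated tablets, are not independent units of a trial that randomises women. The Background gives a reason to expect positive correlation: it attributes about two thirds of implantation failures to reduced endometrial receptivity, which belongs to the woman and is common to both her embryos. With positive correlation the test understates the variance of the between-arm difference, and its P values are too small.

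The mixed model addresses clustering but stops at the centre. A centre intercept is shared by all women at a site and cannot absorb what two embryos of one woman have in common.

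At stake is the reading of one secondary outcome. Implantation lies close to the proposed mechanism in a population defined by implantation failure. A difference declared significant by chance could be taken as mechanistic support even if live birth showed none.

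**Working it through.** **1. The plan's own figure.** No figure is given for implantation. The stated sample size concerns live birth, 30% against 20%, two-sided α = 0.05, power 0.80:

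n per arm = [1.960·√(2·0.25·0.75) + 0.8416·√(0.30·0.70 + 0.20·0.80)]² / 0.10² = (1.2002 + 0.5119)² / 0.01 ≈ 293.2, hence 294 per arm and 588 in total. Then 588 / 0.85 = 691.8, hence 692.

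This reproduces exactly. It is a per-woman calculation and the unit problem does not touch it.

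**2. Inputs for implantation.**
- Embryos per woman: 1 (blastocyst) or 2 (cleavage), from Frozen-thawed embryo transfer.
- Implantation rate: p_c = 0.25 per cleavage embryo and p_b = 0.40 per blastocyst, from the Background. These describe IVF in general and are assumed here.
- Share of women with cleavage transfer, f: not given; 0.5 and 1 are shown.
- Within-woman ICC, ρ: not given; 0.1 to 0.5 is assumed.

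**3. Formula.** Per woman in one arm, under no treatment effect:
- true variance of the sac count, given stage: 2f·p_c(1−p_c)(1+ρ) + (1−f)·p_b(1−p_b)
- variance used by the chi-square test: (1+f)·p̄(1−p̄), with p̄ = [2f·p_c + (1−f)·p_b]/(1+f)

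The ratio V of the first to the second gives a true two-sided size of 2[1 − Φ(1.96/√V)].

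**4. Half of the women cleavage-stage (f = 0.5).** p̄ = (0.25 + 0.20)/1.5 = 0.30. The chi-square variance is 1.5·0.30·0.70 = 0.315. The true variance is 0.1875(1+ρ) + 0.12.
- ρ = 0.1: V = 0.32625/0.315 = 1.036; size 0.054
- ρ = 0.3: V = 0.36375/0.315 = 1.155; size 0.068
- ρ = 0.5: V = 0.40125/0.315 = 1.274; size 0.0825

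**5. All women cleavage-stage (f = 1).** V = 1 + ρ.
- ρ = 0.1: V = 1.10; √V = 1.049; size 0.062
- ρ = 0.3: V = 1.30; √V = 1.140; size 0.086
- ρ = 0.5: V = 1.50; √V = 1.225; size 0.110

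Here the true standard error is about 5% to 22% larger than the naive one. Put the other way, the naive one is too small by 1 − 1/1.049 = 4.7% to 1 − 1/1.225 = 18.4%.

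**6. Checks.** Simulating the chi-square test with 346 women per arm and the 25%/40% rates (200,000 runs per setting) gave 0.054, 0.068 and 0.083 for f = 0.5, and 0.062, 0.085 and 0.111 for f = 1, at ρ = 0.1, 0.3 and 0.5.

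A simpler calculation uses one common embryo rate, with design effect [2f(1+ρ) + (1−f)]/(1+f). It gives sizes of 0.058 to 0.090 at f = 0.5, and the same values as step 5 at f = 1. It is a little higher at f = 0.5 because, when the two stages have different rates and are balanced between arms, the pooled chi-square variance is slightly too large, which offsets part of the inflation. If no woman has two embryos, the excess vanishes; with a common embryo rate it also vanishes at zero correlation.

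**The case against.** The strongest reply concerns scope and size, and much of it stands.

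- **Only one secondary outcome is involved.** Live birth is counted per delivery whatever the number of newborns, and biochemical and clinical pregnancy are per woman. Clinical pregnancy is in effect the woman-level counterpart of implantation and is validly tested. A reader might infer that the trial's main conclusion is at risk; the documents do not support that.
- **The size rests on two unknowns.** With a 50:50 mix and an ICC of 0.1 the error is 5.4% against 5%, which is barely visible. The 11% end requires every transfer to be cleavage-stage with an ICC of 0.5. The protocol stratifies by stage and provides for both, so 11% is a bound and not an expectation. The Background supports a positive correlation but says nothing about its size.
- **Birth weight and congenital anomalies.** Since two-embryo transfers can give twins, one might infer the same error there. The article only lists these outcomes and never fixes the newborn as the unit. The handling of twins may properly sit in the full protocol or analysis plan.
- **Confidence intervals.** The article specifies tests and a P threshold, and no intervals for implantation. An interval built from the same naive variance would be too narrow, but that is a consequence and not something the plan states.
- **Embryo splitting.** Sacs can exceed embryos for an individual woman, so the ratio is not strictly a proportion. The documents give no frequency for this, the test pools embryos by arm, and the point does not depend on it.

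It does not help to say that the detail is left to an unseen analysis plan. The article names the endpoint, the test and the level of the random intercept, and these do not fit together.

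**Conclusion.** The concern holds for implantation rate only. As written, both the chi-square test and the mixed model ignore the correlation between two embryos of one randomised woman, and under positive correlation the P values are too small. For the chi-square test, with an assumed ICC of 0.1 to 0.5 and implantation of 25% per cleavage embryo and 40% per blastocyst, the true size of the nominal 5% test is about 5.4% to 8.3% at an assumed 50:50 stage mix and 6.2% to 11.0% if all transfers are cleavage-stage. Neither the stage mix nor the ICC is in the documents, so these are ranges and not estimates. The issue is moderate: it should be corrected before unblinding, but it leaves the primary comparison, the sample size and the pregnancy outcomes untouched.

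**What to change.** In the Data analysis plan, remove implantation from the outcomes tested by Pearson chi-square. Analyse it with the woman as the cluster: a GEE, or a logistic model with standard errors robust to clustering by woman, adjusted for embryo stage. In the secondary mixed model, account for embryos within a woman when the outcome is implantation, for example with a woman-level random intercept in addition to the one for centre. The per-woman outcomes can stay as planned.

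The cost is a sentence or two and slightly larger standard errors and P values for implantation. No extra data are needed. The Trial status section says that enrolment is ongoing, and allocation stays blinded until the end of the study, so the change can be made without knowledge of the results by arm.
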